## Abstract

**Background:**

Incomplete spontaneous abortions are defined by the intrauterine retention of the products of conception after their incomplete or partial expulsion. This condition may be managed by expectant care, medical treatment or surgery. Vacuum aspiration is currently the standard surgical treatment in most centers. However, operative hysteroscopy has the advantage over vacuum aspiration of allowing the direct visualization of the retained conception product, facilitating its elective removal while limiting surgical complications. Inadequately powered retrospective studies reported subsequent fertility to be higher in patients treated by operative hysteroscopy than in those treated by vacuum aspiration. These data require confirmation in a randomized controlled trial comparing fertility rates between women undergoing hysteroscopy and those undergoing vacuum aspiration for incomplete spontaneous abortion.

**Methods:**

After providing written informed consent, 572 women with incomplete spontaneous abortion recruited from 15 centers across France will undergo randomization by a centralized computer system for treatment by either vacuum aspiration or operative hysteroscopy. Patients will not be informed of the type of treatment that they receive and will be cared for during their hospital stay in accordance with standard practices at each center. The patients will be monitored for pregnancy or adverse effects by a telephone conversation or questionnaire sent by e-mail or post over a period of two years. In cases of complications, failure of the intervention or diagnosis of uterine cavity disease, patient care will be left to the discretion of the medical center team.

**Discussion:**

If our hypothesis is confirmed, this study will provide evidence that the use of operative hysteroscopy can increase the number of pregnancies continuing beyond 22 weeks of gestation in the two-year period following incomplete spontaneous abortion without increasing the incidence of morbidity and peri- and postoperative complications. The standard surgical treatment of this condition would thus be modified. This study would therefore have a large effect on the surgical management of incomplete spontaneous abortion.

**Trial registration:**

ClinicalTrials.gov Identifier: NCT02201732; registered on 17 July 2014.

**Electronic supplementary material:**

The online version of this article (doi:10.1186/s13063-015-0900-1) contains supplementary material, which is available to authorized users.

## Background

Incomplete spontaneous abortions are defined as the intrauterine retention of the products of conception after non-discharge or partial discharge of the egg. After miscarriage, 60 % of women wishing to fall pregnant again are able to do so within 2 years, and 80 % after 5 years [1].

Intrauterine retention after miscarriage is treated by expectant or medical management or surgery [2, 3]. Surgical treatment may be performed immediately or following the failure of expectant or medical treatment. Vacuum aspiration is currently the standard surgical treatment in most centers. However, it is typically carried out in a blind manner, and can therefore lead to the persistence of intrauterine retention, which may not be diagnosed initially. This persistence may be complicated by chronic infection and may require further surgical intervention. The abrasion of the uterine lining that occurs during this blind procedure can also cause simple or complex intrauterine adhesions. The prevalence of these adhesions is around 20 % after curettage for spontaneous abortion [4, 6] and 40 % for repeat procedures [7]. Such adhesions, like chronic endometritis resulting from persistent retention after curettage, may be detrimental to subsequent fertility and require further surgical intervention.

Some studies have reported that hysteroscopy is a beneficial surgical treatment for intrauterine retention after miscarriage, with treated women falling pregnant again within 2 years of the initial intervention in more than 70 % of cases [7, 8]. Hysteroscopy makes it possible to visualize the retention product, its elective removal and the integrity of the cavity directly, without trauma to the adjacent endometrium, while limiting the complications of surgery and the number of repeat interventions due to retention or adhesions, as indicated in a systematic review that retrieved a low frequency of intrauterine adhesions (5.7 %) after the hysteroscopic removal of retained products of conception [9]. Furthermore, hysteroscopy may facilitate the diagnosis of abnormalities or diseases of the uterine cavity (fibroids, polyps), which may be responsible for spontaneous abortions. These abnormalities may be amenable to surgical treatment, improving the management of patients and their prognosis in terms of fertility.

Two retrospective studies have compared the effectiveness of hysteroscopy and curettage for the management of post-abortion and postpartum retention [10, 11]. The first study compared 24 women who underwent curettage with 46 women who underwent hysteroscopic resection. Overall, 20 % of women in the curettage group required secondary hysteroscopy to empty the uterus, whereas no further surgery was required in the hysteroscopy group [10]. Furthermore, the women in the hysteroscopy group fell pregnant more quickly after the intervention than those in the curettage group. The second study, based on a before/after design, compared 42 women who underwent ultrasound-guided curettage with 53 women who underwent hysteroscopy [11]; these 95 women corresponded to 88 cases of failed curettage after miscarriage and seven cases of postpartum retention of the placenta after cesarean section. This study also found that the mean time to conception was shorter among women wishing to fall pregnant again in the hysteroscopy group than in those of the curettage group. Furthermore, despite preliminary curettage in cases of trophoblastic retention, this study also reported that the rate of pregnancy was significantly higher in the hysteroscopy group than in the curettage group (69 % vs 60 %, respectively). Pooling these two studies in a meta-analysis, Smorgick et al. obtained an odds ratio of 1.7 (95 % CI 0.7–3.8, *p* = 0.1) for pregnancy in the hysteroscopy group, with the curettage group used as the reference group [9]. These results provide support for the idea that incomplete spontaneous abortions can be managed by hysteroscopy. However, the retrospective design of these studies, the heterogeneity of the patients included and the low power are such that it is not possible to determine whether hysteroscopy is the best treatment option for intrauterine retention. A randomized, controlled trial is required to evaluate the place of hysteroscopy among the various treatment options.

The main objective of our study is to compare fertility rates between women undergoing hysteroscopy and those undergoing vacuum aspiration for intrauterine retention following miscarriage, in a pragmatic approach. The secondary objectives of the study are: (1) to compare times to conception following the two surgical treatments and (2) to investigate whether hysteroscopy is associated with fewer peri- and postoperative complications and repeat procedures.

## Methods

Items from the World Health Organization Trial Registration Data Set for the Operative hysteroscopy versus vacuum aspiration for incomplete spontaneous abortion (HY-PER) trial are shown in Additional file 1. The TIDieR (Template for Intervention Description and Replication) and SPIRIT (Standard Protocol Items: Recommendations for Interventional Trials) 2013 Checklists are presented in Additional files 2 and 3.

### Study design

The HY-PER trial is a randomized, open, multicenter trial comparing vacuum aspiration with hysteroscopy in women with incomplete spontaneous abortion.

### Ethics

Protocol version 1.1 for this study, dated 06/16/2014, was approved by the “Comité de Protection des Personnes” (CPP) Ile de France XI (no. 14040) and the ANSM (no. 140516B-22). Modified protocol version 2.1 dated 5 June 2015 was approved by the CPP Ile de France XI (no. 14040) on 6 November 2015. Any further modification of the protocol will require approval from the CPP and will be communicated to the local investigators.

### Main outcome

The main outcome is intrauterine pregnancy lasting up to least 22 weeks of gestation in the 2 years after the management of incomplete spontaneous abortion.

### Secondary outcomes

The secondary outcomes are as follows: time to conception; pregnancy outcome: incidence of miscarriage and ectopic pregnancy during the two-year follow-up period; number of surgical complications according to the Clavien-Dindo classification [12]; and the incidence of secondary surgical interventions for the management of intrauterine retention after miscarriage.

### Inclusion criteria

The women included in this study will have the following characteristics:between the ages of 18 and 44 years, covered by the social security system and presenting with trophoblastic intrauterine retention following incomplete spontaneous abortion after the first trimester (<14 weeks of amenorrhea)the pregnancy concerned should correspond to a planned/wanted babydiagnosis of intrauterine retention by transvaginal pelvic ultrasound showing a heterogeneous intrauterine mass or an intrauterine sac over 15 mm thick, with or without endometritisselected by the medical team for surgical management on the basis of local management protocolswritten consent provided.

### Exclusion criteria

The exclusion criteria are as follows:known uterine malformationshistory of surgical treatment for intrauterine retentionintrauterine retention of material over 50 mm thick, diagnosed by transvaginal pelvic ultrasoundemergency hemostatic therapy to treat heavy vaginal bleeding (hemorrhagic miscarriage)presence of an intrauterine deviceongoing pregnancyextra uterine pregnancytrophoblastic retention following an abortion;pregnancy obtained by medically assisted procreation.

### Interventions

The design of the study is summarized in a schematic diagram and a patient flow chart (Fig. 1 and Table 1).

**Fig. 1 Fig1:**
[figure not shown]
Patient flow chart

**Table 1 Tab1:** Time schedule of enrollment

Timetable	Inclusion	Intervention	Postoperative consultation 3 to 8 weeks	Follow up 6 months	Follow up	
					1 year	2 years
Information notice	X					
Written consent	X					
Gynecological examination	X		X			
Transvaginal ultrasound	X					
Randomization	X	X				
Intervention		X				
Recording of adverse effects		X	X	X	X	X
Questionnaire for pregnancy counts				X	X	X

The interventions to be evaluated are operative hysteroscopy (arm A) and vacuum aspiration (arm B) for the management of incomplete spontaneous abortions. These procedures are routinely performed in the participating centers, for various indications, by the local investigators. For both surgical procedures, surgical antibiotic prophylaxis, misoprostol to dilate the cervix, and anti-adhesion barrier gels will be used, according to the routine procedures of each center. In cases of intrauterine retention complicated by endometritis, antibiotic treatment for 48 hours (penicillin, metronidazole, fluoroquinolones or a combination of these antibiotics) will be administered according to the standard practice of each center. The evacuated retention product will be sent for pathological examination. Rhesus-negative women will receive prophylaxis to prevent Rh alloimmunization.

#### Arm A: operative hysteroscopy

Operative hysteroscopy is a routine surgical procedure for the management of intrauterine disease in obstetrics and gynecology departments. The procedure will be performed by a gynecological surgeon, under general or local anesthesia, according to the standard practice of the center concerned, with the patient in the gynecological position. Antibiotic prophylaxis may be administered, according to the standard practice of the center. The cervix is grasped with pozzi forceps and dilated, with up to a size-9 Hegar dilator if necessary, to facilitate insertion of the hysteroscope. The equipment available at the center will be used for operative hysteroscopy. The uterine cavity will be distended with saline or glycine, depending on the polarity of the high-frequency generator required for the resection system (monopolar or bipolar), with a maximum irrigation pressure of 110 mm Hg. The use of energy is usually unnecessary and saline will be the preferred method. Before the operation, the appearance of the uterine cavity will be recorded for diagnostic purposes. The retained conception product will be resected from top to bottom with the surgical resector, without electric power, this being the method recognized as best protecting the endometrium in previous studies [7, 8]. The use of forceps or curettes to facilitate the removal of material is permitted. An electrical current will be used only as a last resort, in cases in which the retained conception product cannot be removed without it. If active bleeding occurs after surgery, elective coagulation via the hysteroscope may be carried out to stop intrauterine bleeding. The distension medium will be measured and examined on entry and exit.

#### Arm B: vacuum aspiration

Vacuum aspiration will be carried out by a gynecological surgeon, according to the standard protocol of the center. A flexible or rigid vacurette may be used. Antibiotic prophylaxis, the diameter of the vacurette used, the extent of cervical dilatation necessary and the use of intraoperative ultrasound guidance will be left to the discretion of the operator and the standard practice of the center. In most centers, the cervix is dilated with a size-9 Hegar dilator for vacuum aspiration. In some centers, the expansion is minimized (in practice, Hegar dilator size 7) to limit the risk of subsequent preterm birth. However, published studies have not reported any benefits of moderate over maximal cervical dilation. The participating centers will therefore be free to carry out cervical dilation according to their standard practices and to use the size and type of vacurette of their choice. In arm A, the use of forceps or curettes to facilitate the removal of material is permitted during the procedure. The scoop of the curette is usually examined to ensure that the uterus is empty at the end of curettage and this practice will be authorized in this trial.

### Examination on inclusion

The initial assessment will include a complete gynecological examination. The patient’s hemodynamic variables (heart rate, blood pressure, temperature) will be recorded and signs of shock sought, to identify women susceptible to hemorrhagic shock in cases of heavy bleeding (exclusion criterion). The last menstrual period of the patient and/or the exact start date of pregnancy in cases in which the pregnancy was dated by early pelvic ultrasound will be recorded. The pelvic examination should include (1) a speculum examination to search for bleeding and to evaluate its extent and source and (2) a vaginal examination to assess pain originating in the uterus or elsewhere.

Incomplete spontaneous abortion will be diagnosed by transvaginal ultrasound performed according to a previously published standard technique for pelvic ultrasound [13]. It must include the median sagittal section of the uterus passing through the endocervical cavity and a section centered on the uterine cavity and passing through the thickest part of the retained conception product, the dimensions of which will be measured. Intrauterine retention will be diagnosed on the basis of the visualization of a heterogeneous intrauterine mass or an intrauterine sac over 15 mm thick.

An ultrasound scan showing a visible intrauterine pregnancy before the expulsion will be required to confirm the intrauterine nature of the pregnancy and to exclude extra-uterine pregnancies. If the intrauterine nature of the pregnancy or its stage cannot be confirmed, β human chorionic gonadotropin (βhCG) levels will be analyzed over 48 hours. A 50 % decrease in βhCG levels over 48 hours will be considered to confirm that the interrupted pregnancy was indeed intrauterine [14]. The intrauterine nature of the pregnancy will be further confirmed by histological analysis of the retained conception product.

Women experiencing hyperthermia or pelvic pain will be examined for endometritis, which may occur as a complication of incomplete miscarriage. Endometritis will be diagnosed according to the criteria in the 2012 guidelines for clinical practice from the French National College of Obstetricians-Gynecologists [15]: the presence of pain following uterine mobilization associated with hyperthermia or high C-reactive protein (CRP) levels, a positive vaginal swab or signs of endometritis on endometrial biopsy. If the blood group of the patient is unknown, rhesus status will be determined and prophylaxis for Rh alloimmunization will be initiated if the patient is Rh-negative.

During this visit, the patient will complete a self-administered questionnaire on her medical history and the lost pregnancy. Details of the protocol will be provided to the patient through a written notice and oral explanations. Signed consent forms will be collected from patients agreeing to participate in the study prior to enrollment, by a senior gynecologist acting as a local investigator in the trial. Informed consent form is shown in Additional file 4.

### Randomization

After the patient has been informed, written informed consent obtained and the criteria for inclusion and exclusion have been checked, a single-blind randomization with a 1:1 ratio will be performed electronically with a secure internet platform, on arrival in the operating room.

The patient will not be informed of the procedure that she has undergone. In addition, the operating rooms will be systematically prepared for hysteroscopy, so that the patient cannot guess the nature of the procedure performed. The intervention will be unblinded if patients experience adverse effects during the study period.

### Intrahospital management

During their stay in hospital, the patients will be managed according to the standard practice of the center. A standardized surgical report will be given to patients included in the study, with no mention of the type of surgical procedure. The patient will then receive a detailed surgical report at the end of her participation in the trial.

### Postoperative consultation

Patients will attend a postoperative consultation within three to eight weeks of the intervention, to check for the absence of complications following the procedure and exposure to pregnancy. Postoperative management, in terms of monitoring, is identical for curettage and hysteroscopy; it should therefore be possible to maintain the single-blind design. If a procedure or special assessment needs to be carried out according to the standard practice of the center (assessment of spontaneous abortion, pelvic ultrasound, diagnostic hysteroscopy) it will be performed without compromising the single-blinded nature of the study. According to amendment of the protocol v2.1 dated 6 May 2015, patients may also be contacted by phone if they do not attend the postoperative consultation, to check for the absence of adverse effects.

### Follow up

After their initial postoperative consultation, patients will attend follow up 6 months, one year and 2 years after surgical treatment or until the successful completion of a subsequent pregnancy. Thus, the length of participation of each patient starts from their inclusion in the study, lasting until subsequent childbirth, or a maximum of 2 years. Each patient will be contacted by telephone. In the absence of a reply, an email and/or a letter will be sent. Subsequent pregnancies, surgical procedures and gynecological findings, such as the diagnosis of abnormal intrauterine pathology (by diagnostic hysteroscopy, hysterosonography, hysterography or pelvic ultrasound) will be recorded. Women will be asked about their exposure to pregnancy (sexual intercourse without contraception), and their use of medical procedures for procreation. The dates of the beginning and the end of any subsequent pregnancies (miscarriage, abortion, ectopic pregnancy, childbirth) will be recorded. The blinding of the study will be assessed during interviews with the patients during follow up. Patients may reply that (1) they do not know which arm they were assigned to, (ii) they think they underwent hysteroscopy, or (iii) they think they underwent vacuum aspiration.

The primary endpoint of the trial is a pregnancy of at least 22 weeks duration in the 2 years of follow up. The progress of the pregnancy will be evaluated according to standard procedures. These data will be collected from a standardized report of the pregnancy and birth (see Additional file 5). In cases of delivery at the same hospital or of additional examinations or surgical procedures, medical records may be used to complete the information.

### Sample size

The mean live birth rate at 2 years after intrauterine retention following miscarriage is 60 % [1]. To demonstrate that the use of hysteroscopy increases this rate by 20 %, i.e., to 72 % with a power of 80 % and α = 0.05 (two-tailed), the number of patients required for this study is 520 (260 per arm) [16, 17]. Assuming that 10 % of patients in each group will be lost to follow up, we plan to include 286 patients in each arm, or 572 patients in total.

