## Discussion

This study is a single-blind randomized controlled trial. The single-blind design was chosen so as to restrict any placebo effect on the occurrence of pregnancy. A double-blind design was not possible because the two arms of the study correspond to surgical interventions. Blinding for the patient will be assessed during follow up, to determine the efficacy of the patient blinding procedure.

The validity and reliability of data collection procedures used in the trial could be called into question as follow up is planned to involve telephone conversations or questionnaires sent by email or post during a 2-year period, rather than a review of medical records. However, patients often move house just before or after giving birth. The patient might then give birth at another hospital and would be lost to follow up. In cases of delivery at the same hospital, medical records could be used to complete the information. Moreover, we took a loss-to-follow-up rate of 10 % into account when determining sample size.

If our study provides evidence that the use of operative hysteroscopy can increase the number of live births in the two-year period following incomplete spontaneous abortion without increasing the incidence of morbidity and perioperative and postoperative complications, then there will be a change in the standard surgical treatment of this condition. This study may therefore have a major impact on the surgical management of incomplete spontaneous abortion.

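### One 60 % figure from one source is called a live-birth rate in Sample size and a conception rate in the Background, so the control rate behind the stated 80 % power is not settled for the 22-week endpoint

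*Protocol article*

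**What the plan says.** Three places in the protocol article bear on the control rate.

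- **Sample size**: "The mean live birth rate at 2 years after intrauterine retention following miscarriage is" 60 %, citing reference 1. The effect follows from it: "To demonstrate that the use of hysteroscopy increases this rate by 20 %, i.e., to 72" %. With 80 % power and two-sided 5 % significance this gives 260 per arm, raised to 286 per arm (572 in total) for 10 % loss to follow-up.
- **Background**: reference 1 is cited for 60 % "of women wishing to fall pregnant again are able to do so within 2 years", with 80 % after 5 years.
- **Main outcome**: "intrauterine pregnancy lasting up to least 22 weeks of gestation in the 2 years after the management of incomplete spontaneous abortion". The Statistical analysis section compares this proportion by chi-squared test in all randomised patients.

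The other rates in the Background are also rates of becoming pregnant. More than 70 % is given for hysteroscopy series, "with treated women falling pregnant again within 2 years of the initial intervention", and 69 % against 60 % for one retrospective comparison. No rate of pregnancies reaching 22 weeks is given anywhere. The Discussion states the hoped-for conclusion as a treatment that "can increase the number of live births in the two-year period", whereas the Abstract states it as pregnancies going past 22 weeks.

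**The concern.** One source, one percentage and one time point are given two meanings. The outcome differs (a live birth or a conception), and so does the denominator (women after retention following miscarriage, or women who want another pregnancy). At least one description is wrong or incomplete, and this figure is the only control-rate input to the sample size.

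If the figure counts conceptions, the direction is clear: fewer women reach 22 weeks within 2 years than conceive within 2 years. Some pregnancies are lost, and a conception late in the second year cannot reach 22 weeks by month 24. The denominator works the same way. The inclusion criteria require that the lost pregnancy was wanted, not that the woman wishes to conceive again, and the primary test is not restricted to women who are trying.

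A 20 % relative increase on a lower control rate is a smaller absolute difference. The trial could then have less than its stated power, and a null result would be read with more confidence than the design supports.

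**Working it through.** **1. The plan's own figure.** Inputs from Sample size: p1 = 0.60, p2 = 0.72, d = 0.12, mean p̄ = 0.66, two-sided α = 0.05, power 80 %.

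Uncorrected: n = [1.960·√(2p̄(1−p̄)) + 0.8416·√(p1(1−p1)+p2(1−p2))]² / d² = [1.960×0.6699 + 0.8416×0.6645]² / 0.0144 = 243.4, so 244 per arm.

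Continuity-corrected: n/4·[1+√(1+4/(n·d))]² with n = 243.4 gives 259.8, so **260 per arm**, as stated. 260 × 1.10 = 286.

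**2. Baseline power at 260 per arm.** Power = Φ{[d√n − 1.960·√(2p̄(1−p̄))] / √(p1(1−p1)+p2(1−p2))}.

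- Uncorrected: (0.12×16.125 − 1.313)/0.6645 = 0.936, so 82.5 %.
- Corrected: replace n by n(1−1/(n·d))² = 260×(1−1/31.2)² = 243.6, so 80.0 %.

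Corrected powers below compare with 80.0 %, and uncorrected powers with 82.5 %.

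**3. Lower control rates.** The documents give no 22-week rate, so these control rates are assumptions. Entries are corrected power (uncorrected in brackets) at 260 per arm.

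| Control rate | 20 % relative increase | 12 points absolute |
|---|---|---|
| 60 % | to 72 %: 80.0 % (82.5 %) | 80.0 % (82.5 %) |
| 57 % | to 68.4 %: 73.9 % (76.8 %) | 78.5 % (81.1 %) |
| 54 % | to 64.8 %: 67.8 % (70.9 %) | 77.3 % (79.9 %) |
| 50 % | to 60 %: 59.7 % (63.1 %) | 76.2 % (78.9 %) |
| 45 % | to 54 %: 50.2 % (53.7 %) | 75.6 % (78.3 %) |

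**4. If the treatment acts on conception.** Take 60 % and 72 % as conception rates at 24 months and convert them to the 22-week endpoint. Twenty-two weeks of gestation is about 20 weeks, or 4.6 months, after conception, so conception must occur by month 19.4. Assume that a share L of conceptions is lost and that each loss takes 3 months out. For a woman with monthly rate λ, P = Σₖ Lᵏ(1−L)·Pr[Gamma(k+1, rate λ) ≤ 19.4 − 3k].

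- *Constant rate*: λ = −ln(0.40)/24 = 0.0382 and −ln(0.28)/24 = 0.0530.
- *Declining rate*: λ varies between women, so that the share not yet pregnant at month t is (1+t/b)^(−a). Fitting 60 % at 24 months and 80 % at 60 months gives a = 1.157 and b = 19.87. Multiplying the rates by 1.660 gives 72 % at 24 months in the hysteroscopy arm.

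| L | Constant: rates, uncorrected power | Declining: rates, uncorrected power |
|---|---|---|
| 10 % | 48.3 / 59.8 %, 75 % | 51.3 / 64.1 %, 84 % |
| 15 % | 46.2 / 57.4 %, 73 % | 49.6 / 62.4 %, 84 % |
| 20 % | 44.0 / 55.0 %, 71 % | 47.8 / 60.5 %, 84 % |
| 25 % | 41.8 / 52.4 %, 68 % | 45.8 / 58.5 %, 83 % |

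A constant rate through 60 % at 2 years implies 1 − 0.40^2.5 = 90 % at 5 years, against the Background's 80 %. The declining rate fits both Background figures and shows no loss from the 82.5 % baseline.

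**The case against.** The strongest defence is that Sample size may describe the source correctly, with the Background merely worded loosely. Every live birth by 2 years has already passed 22 weeks, so 60 % would then be a floor for the endpoint in that population. The 80 % would stand or be slightly conservative: at a 63 % control rate, for example, uncorrected power would be about 88 %. This stands, and it means the documents do not show that the power is overstated.

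A reader might infer that the trial is underpowered, with power near one half. The documents do not support that. It needs the Background to be the correct description, a control rate well below 60 %, and an effect held at 20 % relative. With a 12-point difference the loss is a few points, and with a conception effect under the declining pattern there is none. What keeps the relative case relevant is that Sample size itself states the effect as a proportional increase.

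The denominator gap can also be overstated. Requiring the lost pregnancy to have been planned or wanted selects women likely to try again. It narrows the gap without closing it: the protocol asks about exposure to pregnancy during follow-up and uses it in the time-to-event analysis, but not in the primary comparison.

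Nor is this an arithmetic error, since 260 per arm reproduces exactly.

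**Conclusion.** The point holds as an inconsistent design input of moderate severity. The two sections contradict each other on what the 60 % counts and in whom, neither description is the tested quantity, and the stated 80 % depends on which is right.

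If it is a live-birth rate in a comparable population, the 80 % stands. If it is a conception rate, the control rate for the endpoint is below 60 %, and the consequence depends on the form of the effect:

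- **20 % relative increase held**: corrected power of about 74 % down to 50 % for control rates from 57 % to 45 %.
- **12-point difference held**: about 76–79 % corrected.
- **Conception effect carried through**: about 68–75 % uncorrected with a constant rate, and about 83–84 % with a declining rate that fits the Background.

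The control rates, the share of pregnancies lost and the 3-month gap are assumptions. A marked loss under the conception pattern that fits the Background appears only when the relative increase is held.

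**What to change.** 1. Check what reference 1 counted (conceptions, live births or pregnancies past a given week) and in whom, and make the Background and Sample size agree.
2. State the control rate as the expected proportion of all randomised women with a pregnancy of at least 22 weeks within 2 years, and say how it follows from the source.
3. Keep 572 patients. Replace the single 80 % with power over a stated range of control rates, for example 45–60 %, under both a 20 % relative and a 12-point absolute effect, naming the continuity correction.
4. Word the Discussion's conclusion in terms of the 22-week endpoint, as the Abstract does.

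The cost is a rewritten sample-size paragraph and possibly a less favourable stated power. The endpoint, test, analysis population and recruitment target do not change.

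### The 10 % loss allowance multiplies 260 by 1.10 instead of dividing by 0.90, so 572 women cover a 9.1 % loss, not 10 % (minor arithmetic error)

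*Protocol article*

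**What the plan says.** The Sample size section of the protocol article assumes a 2-year rate of 60 % under standard treatment and 72 % under hysteroscopy, with 80 % power and a two-sided 5 % level. From these it concludes that "the number of patients required for this study is 520 (260 per arm"). It then makes the allowance for loss: "Assuming that 10 % of patients in each group will be lost to follow up, we plan to include 286 patients in each arm", which gives 572 in total.

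The same total is the recruitment target in the Abstract ("572 women with incomplete spontaneous abortion recruited from 15 centers across France"). The Discussion refers to the allowance when it defends follow-up by telephone, e-mail and post: "we took a loss-to-follow-up rate of 10 % into account when determining sample size".

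Two other sections bear on the meaning of the numbers. Statistical analysis names a chi-squared test, without mention of a continuity correction, and analyses every randomized woman by intention to treat. Handling of missing data counts women lost to follow-up by their last known status, and allows for classifying them as failures or for multiple imputation.

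**The concern.** Three figures in one section cannot all hold: 260 needed per arm, 10 % of each group lost, and 286 included per arm. The loss is expressed as a share of the patients in each group, so its natural denominator is the 286 included, not the 260 required. Adding 10 % to the required number is a different operation from allowing for 10 % of the enrolled number to be lost, and it always gives a smaller total.

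What is at stake is consistency more than the trial's ability to answer its question. The recruitment target does not deliver the number that the same section says is required, at the loss rate that the same section assumes.

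**Working it through.** **Inputs (all from the protocol article).** Rates 0.60 and 0.72, two-sided α = 0.05, power 80 %, 260 per arm required, 10 % lost, 286 per arm included (Sample size); 1:1 allocation (Randomization); chi-squared test (Statistical analysis).

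**Step 1: reproduce the 260.** The mean rate is 0.66 and the difference d is 0.12. The uncorrected formula is

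n = [1.960 × √(2 × 0.66 × 0.34) + 0.8416 × √(0.60 × 0.40 + 0.72 × 0.28)]² / 0.12² = 243.4, so 244 per arm.

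With the continuity correction,

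n' = (n/4) × [1 + √(1 + 4/(n × d))]² = (243.4/4) × [1 + √(1 + 4/(243.4 × 0.12))]² = 259.8, so 260 per arm.

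This matches the stated 260 and 520. The other variants tried do not: unpooled 241, arcsine 243, one-sided 192, or 208 with the correction. The base figure is therefore sound, and the discrepancy lies only in the loss step.

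**Step 2: reproduce the 286.** 260 × 1.10 = 286 and 286 × 2 = 572, both as stated.

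**Step 3: apply the stated loss to the stated inclusion.**
- Per arm: 286 × 0.90 = 257.4, which is 2.6 below 260.
- In total: 572 × 0.90 = 514.8, about 515, which is 5 below 520.
- Loss that 572 can absorb before falling under 520: 1 − 520/572 = 9.1 %.
- Inclusion needed for 10 % loss: 260/0.90 = 288.9, so 289 per arm and 578 in total, 6 more than planned. Check: 289 × 0.90 = 260.1.

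**Step 4: power with the number remaining.** The uncorrected power is Φ{[d − 1.960 × √(2 × 0.66 × 0.34/n)] / √[(0.60 × 0.40 + 0.72 × 0.28)/n]}. The corrected version also subtracts 1/n from d.

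| Women per arm with complete follow-up | Continuity-corrected | Uncorrected |
|---|---|---|
| 260 | 80.0 % | 82.5 % |
| 257.4 | 79.6 % | 82.2 % |
| 257 | 79.5 % | 82.1 % |

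On the uncorrected basis 244 per arm suffice, so 286 per arm could absorb a loss of 1 − 244/286 = 14.7 %.

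**The case against.** The strongest reply is that nothing of substance depends on this. The gap is 6 enrolled women, about 1 % of the total, and about half a percentage point of power. That is far less than the uncertainty in the assumed 60 %, 72 % and 10 %. This stands, and it is why the point is minor.

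A reader might infer that the trial falls below 80 % power. The document does not support that. The chi-squared test is named without a continuity correction, and uncorrected it has about 82 % power with 257 per arm. The shortfall is against the stated 520, which is a conservative target for that test.

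A second reply is that intention to treat keeps all 572 women in the comparison, so none drop out of the analysis. It is true that the 515 are women with complete follow-up, not the analysis set. But the Sample size section enlarges the trial because of loss, so its 260 can only mean women whose follow-up is complete. On that logic the enlargement falls short. Equally, dividing by 0.90 secures the stated power only for a comparison of women with complete follow-up, and the document does not make that its primary analysis.

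A reader might also infer that the Discussion misstates the facts when it says that a 10 % loss rate was considered. It does not: an allowance was made, and that sentence does not claim that 260 per arm remain after loss.

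Finally, multiplying by 1.10 is a familiar shortcut. That explains the figure, but does not reconcile it with a loss defined as a share of each group. Nor is this a matter of the article condensing a fuller protocol, since all the conflicting figures are printed in it.

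**Conclusion.** The error is real and minor. The stated inclusion, loss rate and required number are inconsistent: 572 women cover a 9.1 % loss, and at 10 % about 257 per arm (515 in total) would have complete follow-up instead of 260 (520). Power is 79.5 % by a continuity-corrected formula and about 82 % for the uncorrected chi-squared test. The trial is not endangered.

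The inconsistency itself needs only the three printed figures and the reading that the 10 % is a share of the women included in each arm. The power figures also rest on the assumed rates of 60 % and 72 % and on a comparison of women with complete follow-up. That a continuity correction was used is an inference from the exact match at 260, because the article does not name the formula.

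**What to change.** Keep 572 and restate the loss sentence in the Sample size section, for example:

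> 572 women (286 per arm) leave 260 per arm with complete follow-up if 9.1 % are lost. At 10 % loss about 257 per arm remain, giving about 79.5 % power by a continuity-corrected formula (consistent with the stated 260) and about 82 % for the uncorrected chi-squared test.

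This costs one sentence and no additional patients. The Discussion and the Abstract need no separate correction.

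The alternative is to raise the target to 289 per arm, 578 in total. Recruitment was still under way according to Trial status, so this would be feasible. But it changes the approved target, and the Ethics section requires committee approval for any further modification. For a gap of 6 women, restating the figure is the proportionate choice.
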